### Safety and analysis

2.10

Participants will be monitored for undesirable, unintended symptoms, signs, and illnesses. The number and percentage of participants who experience at least 1 adverse event will be calculated and tested using the Chi-squared test or Fisher exact test.

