### Study design

2.1

This randomized, controlled, double-blind, matched-paired clinical trial will compare the pain associated with use of 1 bloodletting device (ROAH-L-NO1) to that associated with a control device (LANZO 1.5). One hundred outpatients will be recruited from the Daejeon University Cheonan Korean Medicine Hospital through advertisements posted on bulletin boards in hospitals. Recruitment commenced in October 2019, and the trial is expected to end in December 2019. One hundred patients who meet the eligibility criteria for this study will be randomly assigned to groups A, B, C, or D. The intervention will begin on the day of the screening visit. Depending on the study group, 2 procedures will be performed, 1 for each participant's hand, in the order of the right and left hand labeled on the bloodletting devices according to the randomization code. The total duration of the clinical trial will be 3 months.

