**Table 2 T2:**

Estimated magnitude of Buzzy effect on pain reduction.

Because the present study will proceed to the point of blood collection, not only the pain intensity is weaker than the previous study, but the duration and intensity of vibration are shorter or weaker than that of Buzzy effect. Therefore, the effect size on the pain reduction of the test device is thought to be smaller than that of Buzzy effect. In the design of the clinical trial, 4 sequences will be assigned, but since the 2 treatments and 2 periods are basically 2 × 2 cross designs, the formula for calculating the sample size corresponding to the design will be applied mutatis mutandis. Assuming that the effect size of the study device is n = (0.61 ÷ 2) ÷ 3,” the sample size (class 1 error *a* = 0.05; power 1 − *b* = 0.8) to be assigned to each device sequence will be as follows: 

Forty-three participants will be required for each treatment group. In addition, considering a 15% dropout rate, the number of participants required per treatment group will be 50. One hundred participants will be calculated as the total number of participants in this study.

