### Randomization and blinding procedures

2.5

There will be 4 assignments according to the order of the bloodletting devices (T = test device, C = control device) and blood collection location (L = left, R = right): RTLC (group A), LTRC (group B), RCLT (group C), and LCRT (group D). Balanced block randomization will be used to evenly assign the participants to each group. The process will be as follows:

1.number the assignment for each group (A = group A, B = group B, C = group C, D = group D),2.randomly select 1 block size among 4, 8, 12, and 16,3.randomly select 1 sequence that can be allocated to 4 groups evenly for each block size,4.assign participants to the selected sequence, and5.repeat steps 2 to 4 for 100 participants.

Participants who meet all registration criteria will be randomly assigned to a randomization identification code (e.g., BCU-R-001, BCU-R-002, …, BCU-R-036) in the order generated by a computer randomized program. The randomization identification code indicates the type of bloodletting device and the order of the left and right hands. Additionally, the participants and the assessors who will be collecting the data will be blinded to the group allocation.

Information of the intervention assignment will be stored in the 3rd statistical department. The randomization code will be placed in an opaque envelope and stored in the hospital. With the exception of disclosure to individual patients in emergency situations, randomization, and blinding will not be disclosed to researchers until the end of the trial.

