### Intervention

2.6

The test device (ROAH-L-NO1) will be manufactured by Roahmed Medical Device Co. (Changwon, Republic of Korea), and the control device (LANZO 1.5) will be manufactured by GMMC Medical Device Co (Seoul, Republic of Korea). Both devices will be applied to the participants’ 3rd finger.

All eligible participants will receive a treatment according to the allocated group, RTLC, LTRC, RCLT, or LCRT, on the day of the screening visit. To maintain the double-blinded nature of the study, during the procedure, a screen will be placed between the participant and the operator. The operator will use the test and control devices on the participants on the outside of the screen, and participants will be indistinguishable to which hand the test device is assigned. The operator will practice using the randomized device on the 3rd finger of 1 hand of the participant. If blood is collected to the extent that the blood glucose level can be measured, it will be determined to be successful, and the 1st measurement will be completed. If no blood is collected, the participant will be checked to confirm no bleeding (“nonbleeding”), and treatment will be applied again after 10 minutes to determine whether blood collection is successful. When the total number of instances of nonbleeding is 3, no further procedure will be recorded, and “blood collection failure” will be recorded. The operator will check the participants’ state of hemostasis after bleeding, and if hemostasis does not occur within 3 minutes (“delayed hemostasis”), the participant will be checked again for complete hemostasis. If hemostasis does not occur for more than 10 minutes, the operator will check the participant for hemostasis abnormalities, and the operator will stop the clinical trial and seek medical attention for the participant. The secondary measurement will be performed 10 minutes after the primary measurement in the same way on the same area of the participants’ opposite hand. Participants will undergo the intervention from 1 to 3 times only on the day of the procedure.

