### Statistical analysis

2.9

Statistical analysis will be primarily based on the principle of the full analysis set. Missing values will be analyzed by the last observation carried forward method. For each of the 2 devices, the VAS score and time at which the participant's pain disappears will be measured, and descriptive statistics will be presented as a mean, standard deviation, median, and minimum and maximum values. The analysis method for evaluation of the variables of efficacy will involve confirmation of the normality of the values and then comparison using the paired *t* test or Wilcoxon signed-rank test. The McNemar test will be used to analyze the VRS score, total number of nonbleeding cases, number of blood collection failures, number of cases of delayed hemostasis, and number of participants. The significance level will be set at *P* < .05 and the confidence interval at 95%. All statistical analyses will be performed using SPSS Statistics for Windows version 20.0 (IBM Corp, Armonk, NY).

If necessary, subgroup analyses of outcome variables, such as the demographic variables measured at baseline (e.g., sex, age, duration of illness, treatment expectation) can be performed. Safety assessments will be performed primarily by analyzing the frequency of adverse events and serious adverse events (SAEs) that researchers suspect to be related to treatment. The collected safety data will be summarized appropriately. All adverse events that occur will be listed with a detailed description. All SAEs will be recorded descriptively. The adverse events will be collected through patient symptom reporting and researcher observation. The frequency of each adverse event associated with or unrelated to the intervention will be recorded and analyzed using descriptive statistics. There is no intermediate analysis of this study, and the final decision regarding the completion of the clinical trial will be made by the PI.

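### Adverse events are to be tested by chi-squared or Fisher exact test, although every randomised sequence gives each participant both devices

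*Protocol article*

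**What the plan says.** The design is paired throughout the protocol article. Section 2.1 opens with "This randomized, controlled, double-blind, matched-paired clinical trial will compare the pain associated with use of 1 bloodletting device" against a control device, and adds that "2 procedures will be performed, 1 for each participant's hand". Section 2.6 says the second measurement "will be performed 10 minutes after the primary measurement in the same way on the same area" of the opposite hand. Section 2.5 states "There will be 4 assignments according to the order of the bloodletting devices" and the hand; the four are RTLC, LTRC, RCLT and LCRT, and each includes both T and C. The sample size in section 2.4 is argued on the same footing: "since the 2 treatments and 2 periods are basically 2 × 2 cross designs".

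For event-type outcomes section 2.9 names a paired test: "The McNemar test will be used to analyze the VRS score, total number of nonbleeding cases", and the same for collection failures and delayed hemostasis. On adverse events, section 2.9 says: "The frequency of each adverse event associated with or unrelated to the intervention will be recorded and analyzed using descriptive statistics".

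Section 2.10 then adds a significance test, on counts and percentages: "participants who experience at least 1 adverse event will be calculated and tested using the Chi-squared test or Fisher exact test". It does not say which groups are compared.

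**The concern.** Used to compare event proportions, the chi-squared and Fisher tests assume that the two proportions come from different, independent people. Here the test-device and control-device observations come from the same person, 10 minutes apart. Someone prone to bruising or prolonged soreness is likely to show it on both hands, so the two outcomes will tend to be positively correlated. An unpaired test ignores this and uses a standard error that is too large.

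The Abstract names identifying the safety of the device as an aim. An analysis that is too conservative errs in the unhelpful direction for safety: a real excess of local events with one device is more likely to be reported as no significant difference.

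The article also disagrees with itself. Delayed hemostasis, a per-hand event with a safety character, gets a paired test in section 2.9, while other adverse events in the same people get an unpaired one in section 2.10.

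**Working it through.** **Which groups could the test compare?** Three readings are possible.

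1. Test hand against control hand. This counts 100 people as 200 independent observations.
2. Sequence A against B, C and D. These groups are independent, so the test is formally valid, but every sequence contains both devices. The result would concern order and side.
3. Participants with any event, not split by device. Then there is no device contrast to test.

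None of the three gives a sound device comparison.

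**Inputs.** n = 100 participants (sections 2.1 and 2.4); significance level 0.05 (section 2.9), taken as two-sided. The article gives no adverse-event rates, no within-person correlation and no design figure for the safety test, so there is nothing of its own to reproduce. The rates and correlations below are assumptions.

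**Standard error.** With equal event rates and within-person correlation ρ, the unpaired standard error exceeds the paired one by the factor 1/√(1 − ρ):

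- ρ = 0: 1.00
- ρ = 0.3: 1/√0.7 = 1.20
- ρ = 0.5: 1/√0.5 = 1.41

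**Illustrative table.** Events on both hands 10, test hand only 12, control hand only 3, so 22/100 against 13/100.

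- Implied correlation: (0.10 − 0.22 × 0.13)/√(0.22 × 0.78 × 0.13 × 0.87) = 0.0714/0.1393 = 0.51.
- Unpaired SE: √[(0.22 × 0.78 + 0.13 × 0.87)/100] = 0.0534.
- Paired SE: √{[15/100 − (9/100)²]/100} = 0.0377. The ratio is 1.42.
- Chi-squared without correction: pooled rate 35/200 = 0.175; 0.09²/(0.175 × 0.825 × 2/100) = 2.81, p = 0.094.
- Fisher exact: p = 0.136.
- Exact McNemar on 12 against 3: 2 × P(X ≤ 3), X ~ Bin(15, 0.5), = 2 × 576/32768 = 0.035.

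The same data cross 0.05 under the paired test and not under either test named in section 2.10.

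**Simulation.** 40,000 simulated trials per scenario, 100 participants, correlated paired binary outcomes, two-sided 0.05.

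| Scenario | ρ | Chi-squared | Fisher | McNemar | Exact McNemar |
|---|---|---|---|---|---|
| Type I error, 20% vs 20% | 0 | 0.053 | 0.034 | 0.053 | 0.032 |
| | 0.3 | 0.020 | 0.011 | 0.053 | 0.029 |
| | 0.5 | 0.006 | 0.003 | 0.049 | 0.029 |
| Power, 30% vs 15% | 0 | 0.73 | 0.67 | 0.72 | 0.66 |
| | 0.3 | 0.77 | 0.70 | 0.88 | 0.82 |
| | 0.5 | 0.80 | 0.73 | 0.96 | 0.94 |

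Equal rates of 10% and 30% give nearly the same type I error for chi-squared: 0.019 to 0.021 at ρ = 0.3 and 0.006 to 0.007 at ρ = 0.5.

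**The case against.** The strongest reply is that section 2.10 does not say what is compared. The unpaired hand-by-hand analysis is an inference, and the four sequence groups are genuine independent groups. That is so, but the only reading on which the test is valid does not compare the devices. What does not exist is an independent group for each device.

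Second, section 2.9 treats safety mainly through frequencies, listings and description, and gives delayed hemostasis a paired test. This limits how much depends on section 2.10. It does not make the named test suitable, and it leaves one section describing adverse events and the next testing them.

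Third, the gain from pairing depends on assumed figures. Local events in 22% and 13% of hands may be high for a fingerstick. With few events the paired test offers little: for 1 on both hands, 4 test only and 1 control only, exact McNemar gives p = 0.38, chi-squared 0.25 and Fisher 0.44. With five or fewer discordant pairs exact McNemar cannot reach 0.05, because 2 × 0.5⁵ = 0.0625. At ρ = 0.3 its power gain over chi-squared in the 30% vs 15% scenario is only about 5 points (0.82 against 0.77). All of this stands and limits the size of the effect. The error is also conservative, so it does not create false positives.

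Fourth, not everyone will receive both devices. Sections 2.3 and 2.6 allow a participant to stop after three nonbleeds on one finger or after failed hemostasis. Such people form no pair and would drop out of a McNemar test, so the fix must say how they are reported.

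**Conclusion.** The point holds. Section 2.10 names a test for independent groups in a within-person trial, and no reading makes it a valid comparison of the devices. This is a stated choice that does not fit the design, not a detail left to a fuller document.

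The size depends on two figures that the article does not give. With positive within-person correlation the unpaired test is too conservative: at ρ = 0.3 to 0.5 its standard error is overstated by about 1.2 to 1.4 and chi-squared type I error falls from 0.05 to between about 0.02 and 0.006. In the 30% vs 15% scenario, power falls by about 11 to 16 points for chi-squared against McNemar, and by about 11 to 21 points for Fisher against exact McNemar. At zero correlation, or with very few events, the choice of test makes little practical difference.

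The efficacy analyses are unaffected. The change should be made because safety is a stated aim and the remedy is small.

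**What to change.** - Record each local adverse event against the hand, and hence the device, on which it occurred. If the case report form already does this, nothing needs adding.
- Replace the test in section 2.10. Compare the number of participants with at least one event on the test hand with the number on the control hand by exact McNemar, and report the paired risk difference with a 95% CI. If few events are expected, the interval and the counts matter more than the p-value.
- List events in participants exposed to only one device separately, by device, so that they are not lost from a complete-pair analysis.
- Report systemic events, which cannot be assigned to a hand, descriptively by device order.
- Reconcile sections 2.9 and 2.10 so that it is clear which adverse-event summaries are descriptive and which are tested.

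The cost is a few sentences of analysis wording and, at most, one field on the adverse-event form. The hand should be recorded when the event is reported, because it is hard to recover reliably later.

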### Ethics

2.11

This study is designed based on the Helsinki Declaration and the Korean Clinical Practice Guidelines, and it has been approved by the Korean Institutional Review Board of DUCKMH (approval number DJUMC-2019-MD-01-1). This study protocol is registered with CRIS (CRIS-KCT0004478). All participants will receive a full written explanation of the study's protocol and an informed consent form. Participants may be required to quit the study in case of SAEs or adverse drug reaction, and then they will be reported to the institutional review board of the hospital. All participants of this study will be allowed to withdraw their consent at any time for any reason or discontinue their participation on a voluntary basis.

## Discussion

3

The bloodletting device is a medical device used for medical examination by a medical institution or for diabetic patients to measure blood glucose levels. Diabetic patients are the second most common group after medical institutions for whom the bloodletting device is used. According to statistics released by the World Health Organization, the number of diabetic patients worldwide reached 422 million in 2014, with a 7% to 8% increase in the disease annually.^[7–10]^ This group of patients draws blood for themselves, 2 to 3 times a day, to measure their blood glucose levels. Pain during blood collection has caused about 50% of diabetic patients to stop monitoring their own blood glucose levels.

Human skin is classified into the epidermis, dermis, and subcutaneous tissue. For blood collection, the needle only needs to enter the capillaries, that is, just before the subcutaneous tissue.^[11]^ If the needle penetrates too deep, it causes severe pain, so it is usually necessary to reduce the pain by adjusting the depth of the needle. However, all pain appears when the stimulus is applied to the skin and the stimulus signal is transmitted to the femoral cortex. Therefore, no matter how short the needle is, if the needle enters the skin directly, the pain is felt by the patient and a true painless effect cannot be obtained.

For this study, we prepared a bloodletting device using the principle of prestimulation neurodisturbance and planned a randomized clinical trial to evaluate pain during blood collection. However, bias may occur because this trial will be conducted without a pilot study. Nevertheless, this study may provide insight into the underlying mechanisms of the pain-reducing effect of the developed bloodletting device, and can lay the groundwork for further research on the development of painless bloodletting devices.
